### Control Group

The Control Group will continue with their usual program and will receive the intervention training and materials at the end of follow-up assessments.

### Assessment of the Outcomes

Data collection will occur at baseline (before randomization) and at the end of the intervention (Fig. 3 Participants Timeline). For those children who have turned 3 at follow-up, an additional four executive function tasks will be collected as described below. Trained research assistants blinded to group allocation will collect all data.

**Fig. 3 Fig3:**
[figure not shown]
Effects of reduced sitting time on toddlers’ cognitive development: a cluster randomized controlled trial. Participants Timeline

#### Primary Outcome

##### Cognitive development

Cognitive development and executive functions will be assessed using the cognitive sub-test from the Bayley Scales of Infant and Toddler Development—Third edition (Bayley-III) [59]. This sub-test assesses sensorimotor development, exploration and manipulation, object relatedness, concept formation, memory, and problem solving. The Cognitive subset of the Bayley scales will be applied and scored according to standard procedures described in the Bayley-III manual for the age of the child at the starting point. For those children who have turned 3 at follow-up, an additional four executive function from the Early Years Toolbox will be used to ensure assessments are comprehensive. These iPad-based tasks assess the three core aspects of EF, and have been developmental and psychometrically evaluated with large samples of preschool-aged children [60]. All iPad apps have built-in auditory instructions so the data collectors could ensure the participant understood the instructions, clarified where necessary and remained on task.

The Early Years Toolbox go/no-go task [61] evaluates the ability to inhibit a dominant behavioural response in response to a less frequently presented ‘no-go’ stimulus. In this game, a child is asked to ‘catch the fish’ by tapping on the screen when they appear (‘go’ response) and ‘avoid the sharks’ by not pressing anything when the less-frequent sharks appear (‘no-go’ response). The task is evenly split into three mixed blocks of 25 stimuli, each consisting of 80 % ‘go’ trials, so as not to exceed 1 min for each block and to provide participants with a short break between each block. Animated stimuli (swimming from left to right across the screen) are presented in random order for 1500 ms each, followed by a 1000 ms interval between stimuli. Scores represent the product of proportional go and no-go accuracy.

The Early Years Toolbox [name] task assesses visual-spatial working memory, or the amount of visual information that concurrently can be activated in the mind. The child is presented with an image of a cartoon ant, which has coloured dots on different spatial locations on his body. [name], with his coloured dots, is presented for five seconds, followed by a blank screen for four seconds, and then an image of [name] without any coloured dot appears and the participant indicates the recalled locations by tapping on the recalled locations. In the first level, with a single dot, children must remember a single spatial location. The task proceeds until the earlier of failure on all three trials at a given level of difficulty or level eight (with the location of eight coloured dots to recall). Performance is indexed by a point score, such that each successive level with at least two trials correct receives 1 point, and all correct trials thereafter receive 1/3 of a point.

The third Early Years Toolbox task, a card sorting task, is a measure of cognitive flexibility (the ability to disengage and re-direct attention) [61]. In this task, children are presented with stimuli, one at a time, which vary in shape and colour (red rabbit and a blue boat). Children are asked to sort the shapes into castles (denoted by a blue rabbit and red boat) first by one dimension (colour) and then, after six trials, by another dimension (shape). Successful completion of at least five pre-switch and post-switch trials results in administration of a border version of the task, in which children must flexibly switch between these sorting rules depending on whether the stimulus does or does not have a border. Scores represent the number of correct trials once the initial switch has been made.

Cognitive assessments and EF tests will be conducted individually in a private area and will be scheduled on separate days, where possible, to minimise cognitive fatigue.

#### Secondary Outcomes

##### Sitting time

Total time spent sitting and bouts of sitting during childcare hours will be assessed over a 1 week period using an activPAL accelerometer [62]. The activPAL (PAL technologies, Glasgow) is small (53 x 35 x 7 mm) and lightweight (15 g) and is placed on the front of the upper thigh (using a small hypo-allergenic adhesive gel patch, and covered with a transparent sticky film to secure it) allowing it to measure different postures (eg, sitting, standing). Concurrent and criterion validity of the activPAL for sitting time measures, as well as for interruptions (breaks—defined as the number of transitions recorded from “sit/lie” posture to “stand”) in SB have been established for young children [62–64].

##### Physical activity and sedentary time

Levels of physical activity and sedentary time over a usual week will be measured using Actigraph GT3X+ accelerometers. Actigraphs are small, light and unobtrusive devices worn on a belt around the waist. These accelerometers have established validity and utility in toddlers [65, 66]. These devices can collect very high-frequency raw data (30 Hz), which will be reintegrated and analysed according to best-practice methodologies at the time of analysis. Participants will be asked to wear the accelerometer for 24 h/day over 7 days (except for water activities), and parents will be asked to register in an activity monitor log the times that the accelerometers was removed from the child.

##### Demographics

Demographic and family lifestyle variables will be assessed with a family survey. This survey will include the following variables: parents/caregiver’ age, gender, marital status, Indigenous/Torres Strait Islander origin; child’s gestational age at birth; family structure and family socio-economic status. Family socio-economic status will be assessed by the family postcode address using the Australian Socio-economic Indexes for Areas 2011 (SEIFA-Index of Relative Socio-Economic Disadvantage) [53] and also with a modified version of the Graffar index [67] which includes the highest level of schooling completed, income, main source of income and type of employment (job title). The family survey will also assess parental height and weight and smoking and alcohol habits [68, 69].

##### Sleep

Sleeping patterns will be assessed with the Tayside Children’s Sleep Questionnaire [70, 71]. This 10-item scale evaluates the child’s ability to initiate and maintain sleep. The family survey also asks parents to report their child’s total sleeping time per day. Sleep duration will also be objectively measured with the Actigraph GT3X+ accelerometers.

##### Psychological adjustment

Educators will assess children’s psychological adjustment with the extended version of the Strengths and Difficulties Questionnaire (SDQ). This questionnaire asks about the emotional symptoms, conduct problems, hyperactivity-inattention, peer problems and pro-social behaviour of the child [72, 73].

##### Anthropometrics

We will measure weight, height and waist circumference according to standard procedures [74]. Body height will be measured to the nearest 0.1 cm in bare or stocking feet with the child standing upright against a portable stadiometer (Seca 254 Hamburg, Germany). Body weight was measured to the nearest 0.10 kg, lightly dressed (and without diapers) using a portable electronic weight scale (Seca 254 Hamburg, Germany). Waist circumference will be measured with a non-elastic tape at the top of the iliac crest [75, 76].

##### Blood pressure

Blood pressure will be measured with a digital vital signs monitor using an appropriate size cuff (WelchAllyn PROBP 3400 series, Skaneateles Falls, NY: USA), in a quiet room between 7 and 9 a.m. Two measurements will be taken after 5 and 10 min of rest with the participant in a sitting position, with the arm relaxed and supported so that the cubital fossa is at the level of the heart. Measurements will be taken from the right arm using an appropriate cuff size. A third measurement will be taken if the difference between the previous two measurements was more than 2 mm Hg [77–79].

##### Retinal microvasculature

Changes in the retinal micro-vessels are believed to precede chronic conditions such as heart disease and diabetes [80, 81]. Retinal microvasculature will be assessed by retinal photography, as a direct and non-invasive visualization of the body’s microvasculature. The image of each eye will be recorded using a portable retinal camera (Optomed Smartscope Pro, Finland) according to the manufacturer instructions. The child will be asked to look into the camera and focus on the red dot that will be floating in their visual space. Once the eye is focused and in the right position, a photo will be taken of each eye [82]. Images will be analysed for arterial and venular diameters, arteriovenous ratio and vessel tortuosity using appropriate software.

##### Bone mineral density

Bone mineral density will be assessed using a portable ultrasound bone sonometer (Pediatric Sunlight MiniOmni, BeamMed Ltd., Israel) which non-invasivly measures bone speed of sound (in meters per second). Results and then expressed as age- and gender-matched Z-scores and percentiles. The measurements will be performed on the left leg at the mid-tibia (point between the apex of the medial malleolus and the distal patellar apex), while the participant and the operator are comfortably seated, according to the protocols recommended by the manufacturer (www.beammed.com).

##### Mother’s health during pregnancy

The family survey will assess several variables about the mother’s health during pregnancy that are known to be related with our primary outcome and/or cardiovascular health of the children. We will assess weight gain during pregnancy [83], weeks of gestation [84], type of birth delivery (vaginal delivery, instrumental vaginal delivery or caesarean) [85, 86], singleton and multiparous pregnancy [87], health problems during pregnancy (Hypertension or Pre-eclampsia, Gestational Diabetes, Type II Diabetes, Type I Diabetes, Vitamin D deficiency, Anaemia, Cardiovascular disease, Thyroid dysfunction) [88–92] smoking and alcohol consumption during pregnancy [93], vitamins supplementation and physical activity habits [94].

##### Educators’ demographics and self-efficacy

Educator’ age, gender, level of schooling, qualification and years of experience will be self-reported. Educators will also complete a modified version of the teacher self-efficacy scale of Bandura [95]. The questionnaire will assess instructional self-efficacy; disciplinary self-efficacy and self-efficacy to create a positive childcare climate.

##### Childcare environmental rating

We will rate ECEC centres with the Infant/Toddler Environment Rating Scale-revised edition (ITERS-R). This scale is designed to assess the structural and process quality of early childhood programs. The scale contains 39 items that comprise seven subscales: (i) space and furnishings; (ii) personal care routines; (iii) listening and talking; (iv) activities; (v) interaction; (vi) program structure; and (vii) parents and staff [96].

### Sample Size

#### Sample size and power calculations

We anticipate an effect size of 0.5 for the between-group difference in cognitive development and an intraclass correlation (ICC) of 0.01–0.05. The proposed design has 16 services (8 per group) and 16 children completing per service. Allowing for participation of 18 eligible children with two dropouts per service [10 %] gives a total sample size of 256. This reduces to an effective sample size of 200–254 (with rounding) based on ICCs of 0.05−0.01. The power to detect an effect size of 0.5 with these sample sizes ranges from 0.87–0.96 at an alpha level of 0.05.

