### Statistical analysis

#### Primary analysis

Analysis of the primary outcome will be conducted using a linear or generalized mixed model in STATA 14.0 (or higher). The mixed model will contain a random effect for time and service nested within group. Degrees of freedom will be altered manually in the code to adjust for the effect of clustering. These established procedures are well documented by Murray [97] and have been used previously by our research institute to analyse a similar study in primary schools [98]. No interim analyses are planned.

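### The effective sample size of 200–254 does not follow from the stated ICCs and cluster size, does not yield the stated power, and the power makes no visible allowance for the 14 cluster-level degrees of freedom

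*Protocol article*

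**What the plan says.** All the inputs stand in the protocol article under Sample size and power calculations.

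- Effect: "We anticipate an effect size of 0.5 for the between-group difference in cognitive development".
- Clustering: "an intraclass correlation (ICC) of 0.01–0.05".
- Design: "The proposed design has 16 services (8 per group) and 16 children completing per service".
- Attrition: "Allowing for participation of 18 eligible children with two dropouts per service", printed as 10%, which "gives a total sample size of 256".
- Effective size: "This reduces to an effective sample size of 200–254 (with rounding", with 200 belonging to ICC 0.05 and 254 to ICC 0.01.
- Power: "The power to detect an effect size of 0.5 with these sample sizes ranges from 0.87–0.96 at an alpha level of 0.05".

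Under Primary analysis the article adds: "Degrees of freedom will be altered manually in the code to adjust for the effect of clustering". It prints no number of degrees of freedom. The sample size paragraph does not name the test used for power, does not say whether alpha is one- or two-sided, and claims no gain from baseline adjustment or repeated measurement.

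**The concern.** The paragraph gives everything needed to recompute its own result, and two checks fail. The effective sizes are far too large for the stated ICCs and cluster size, by more than rounding can explain. The power is then attributed to those effective sizes, yet it is lower than they would produce.

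A third point concerns the link between planning and analysis. The primary analysis is to reduce its degrees of freedom for clustering. With only 16 services that reduction costs power, and the printed power looks like that of a calculation without it.

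This is the power statement for the primary outcome. If power at the upper planning ICC is nearer 0.80 than 0.87, the risk of missing the hypothesised effect is about 0.20 rather than 0.13. Readers would then credit the trial with more sensitivity than it has, and planners of later childcare trials might reuse an effective sample size that is wrong.

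**Working it through.** **Inputs** (protocol article, Sample size and power calculations): 16 services, 8 per group; m = 16 completers per service; N = 16 × 16 = 256; effect d = 0.5 SD; ICC 0.01 and 0.05; alpha 0.05. Two-sided testing is my assumption. Allocation is 1:1 (Randomisation and allocation).

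**Step 1. Effective sample size.** Design effect DE = 1 + (m − 1) × ICC; effective size ESS = N / DE.

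| ICC | DE | ESS | Printed | Printed / computed |
|---|---|---|---|---|
| 0.01 | 1 + 15 × 0.01 = 1.15 | 256 / 1.15 = 222.6 | 254 | 1.14 |
| 0.05 | 1 + 15 × 0.05 = 1.75 | 256 / 1.75 = 146.3 | 200 | 1.37 |

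The gaps are about 31 and 54 children. Solving backwards, ICC = (256 / ESS − 1) / 15, so 254 would need an ICC of 0.0005 and 200 an ICC of 0.019.

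**Step 2. Attempts to reproduce the printed pair.** I varied N (256 or 288 enrolled), m (16 or 18) and the design effect (1 + m × ICC, or its square root). None gives 200 and 254 together. The nearest at the upper end, N = 288 with m = 16, gives 250 at ICC 0.01 but only 165 at ICC 0.05. The nearest at the lower end, the square root of the design effect with N = 256, gives 194 but 239 at the upper end.

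**Step 3. Power from the printed effective sizes.** The noncentrality is d × √(ESS / 4).

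- ESS 200: 0.5 × √50 = 3.54, power 0.94.
- ESS 254: 0.5 × √63.5 = 3.98, power 0.98.

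These hold for the normal test and for the t test on ESS − 2 df. One-sided they rise to 0.97 and 0.99. On 14 df they are 0.91 and 0.96. No version gives 0.87 from an ESS of 200.

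**Step 4. Power from the correct effective sizes**, d = 0.5, two-sided 0.05:

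| ICC | ESS | Noncentrality | Normal | t, ESS − 2 df | t, 14 df | Printed |
|---|---|---|---|---|---|---|
| 0.01 | 222.6 | 3.73 | 0.962 | 0.960 | 0.934 | 0.96 |
| 0.05 | 146.3 | 3.02 | 0.856 | 0.852 | 0.803 | 0.87 |

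The 14 is derived: 16 services − 2 groups. The printed power lies within 2 percentage points of the large-sample columns and is clearly above the 14 df column. The likeliest reading is that the effective sizes are the wrong figures, and that the power was worked out from roughly correct ones without a degrees-of-freedom allowance.

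**Step 5. Minimum detectable effect** for 80% power on 14 df: 0.40 SD at ICC 0.01 and 0.50 SD at ICC 0.05. The latter equals the hypothesised effect.

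**Step 6. Attrition.** 16 × 18 = 288 enrolled; 2 / 18 = 11.1%, printed as 10%.

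**The case against.** The strongest reply is that the number a reader acts on, the power, is nearly right. With the correct effective sizes a large-sample test gives 0.85–0.96 against the printed 0.87–0.96, so the slip could be confined to an intermediate figure. That is fair as far as it goes. It holds, however, only before the degrees-of-freedom adjustment to which the article commits its own analysis, and the printed effective size is wrong on any reading.

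Second, the degrees-of-freedom point is partly inference. The article prints neither 14 nor the test behind the power figures. That stands: 14 is the natural value for a group effect judged against variation between services, and the omission is inferred from numerical fit. It is also a matter of planning, since the analysis itself does address clustering.

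Third, the outcome is measured at baseline too, which could recover power. As an illustration only, if baseline entered as a covariate with correlation r = 0.3 to 0.5 at every level, ESS at ICC 0.05 would be 146.3 / (1 − r²), that is 160.8 to 195.0, and power on 14 df 0.84 to 0.90. If change scores were compared instead, ESS would be 146.3 / [2(1 − r)], a loss whenever r is below 0.5. The article gives no correlation and claims no such gain, so 0.80 is the figure its printed inputs support, not a bound on what the trial might achieve.

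Finally, the design is not endangered. Power stays at about 0.80 or more across the stated ICC range, and a null result should in any case be read from its confidence interval. This limits the consequence but does not make the printed figures consistent.

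**Conclusion.** The concern holds. On the article's own inputs the effective sample size is 223 (ICC 0.01) to 146 (ICC 0.05). The printed 254 and 200 overstate it by 14% and 37%. The printed effective sizes and the printed power also cannot both be right, because 200 would give about 0.94 rather than 0.87. These two conclusions are arithmetic; the second does not depend on the choice of test or sidedness.

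On 14 degrees of freedom, power for 0.5 SD is 0.93 to 0.80, and type II error at ICC 0.05 is about 0.20 against the implied 0.13. This part assumes two-sided testing, equal service sizes, 14 as the cluster-level degrees of freedom and no gain from baseline. Even without the degrees-of-freedom allowance the lower end is 0.85. At ICC 0.05 nothing is held in reserve for unequal service sizes or for fewer than 16 completers per service; I have not quantified those losses.

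**What to change.** Restate the sample size paragraph along these lines: 288 children enrolled and 256 completing (11% dropout); design effect 1.15 to 1.75 for ICC 0.01 to 0.05; effective sample size 223 to 146; two-sided power for 0.5 SD at alpha 0.05 of 0.93 to 0.80 on 14 degrees of freedom, or 0.96 to 0.85 if a large-sample test is assumed. Name the test and the degrees of freedom. If a gain from the baseline measurement is to be claimed, give the assumed correlation and the power with and without it.

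The cost is a correction to one paragraph and a slightly less favourable power statement. Enrolment, number of services, allocation and analysis stay as they are.

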### Randomisation and allocation

Research assistants will conduct baseline assessments before randomization. ECEC services will be randomly allocated to either intervention or control condition. We will create a randomization sequence using excel 2011 (Microsoft, Redmond, WA, USA) with a 1:1 allocation using random block sizes of 2, 4 and 6. An independent statistician will conduct this procedure and the data manager will perform the random allocation of services.

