## Methods

### Study design

We will implement a 12-months 2-arm parallel group cluster randomised controlled trial. Cluster randomization was chosen for practical reasons and to prevent contamination. The selection of the ECEC services (clusters) will be based on the ECEC’ postcode using the Australian Socio-economic Indexes for Areas 2011 (SEIFA-Index of Relative Socio-Economic Disadvantage) [53]. We will consider the centres belonging in the first and second quartile of this Index (extreme-low and moderate-low socio-economic status) in the Illawarra Region, NSW, Australia. Eight services will be randomly allocated to the intervention group and eight to the control group.

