#### Recruitment

After determining the eligible ECEC services, we will perform a simple randomisation using a computerised sequence generation to determine the order in which eligible ECEC services will be invited to participate in this study. Invitations will be performed by email and by phone, requesting a face-to-face meeting with service Director to outline the aims and procedures required for this RCT.

If a selected ECEC service declines participating in the study, an additional phone call and face-to-face meeting will be made to the next eligible service on the list until 16 childcare services agree to participate in this RCT.

All toddlers enrolled in each class/ECEC centre will be invited to participate in the study. We will send an invitation letter and an information sheet outlining the aims and procedures of the study to the toddler’s parents or guardians. While no exclusion criteria will be applied for participation in the study, to prevent any discrimination, for analysis and reporting only toddlers eligible according to the aforementioned inclusion criteria will participate in the study.

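### The block scheme as described does not ensure the 8:8 split of services (minor), and the allocation makes no use of the SEIFA quartile already known for every service

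*Protocol article*

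**What the plan says.** - Study design fixes the split: "Eight services will be randomly allocated to the intervention group and eight to the control group". Sample size and power calculations relies on it: "The proposed design has 16 services (8 per group) and 16 children completing per service".
- Randomisation and allocation describes the method: "ECEC services will be randomly allocated to either intervention or control condition", "with a 1:1 allocation using random block sizes of 2, 4 and 6". It does not say that the blocks are chosen to total 16, and it names no stratification, matching or other restriction. Baseline assessments come before randomisation.
- Study design uses the SEIFA disadvantage index, by service postcode, to define eligibility: "We will consider the centres belonging in the first and second quartile of this Index". It labels the two levels extreme-low and moderate-low. The number of services expected from each is not given.
- Recruitment invites services in random order, one after another, "until 16 childcare services agree to participate in this RCT". There is no quota by quartile.
- Primary analysis describes a mixed model with terms for time and for service nested within group. No socio-economic term is named.

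**The concern.** Two features of the allocation deserve attention when only 16 units are randomised.

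First, permuted blocks guarantee equal arms only if the last block is complete. Blocks of 2, 4 and 6 drawn freely need not end at 16. A list cut off there can give 9:7 in either direction, which is not the design that was powered.

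Second, blocking balances the number of services, not their characteristics. The Background ties socio-economic disadvantage to cognitive development, which is the primary outcome. The service-level quartile is held before any service is allocated. Without balancing, one arm can by chance receive most of the more disadvantaged services. Recruiting more children within the same 16 services would not repair that, because quartile varies between services.

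**Working it through.** **Inputs from the article.** 16 services, 8 per arm, 16 completing children each; 1:1 allocation with blocks of 2, 4 and 6; effect size ("We anticipate an effect size of 0.5 for the between-group difference in cognitive development"); "an intraclass correlation (ICC) of 0.01–0.05"; alpha 0.05, taken here as two-sided.

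**Assumptions not in the article.** Each block size has probability 1/3, draws are independent, and the list is cut at 16. Eight services fall in each SEIFA quartile; 6/10 and 4/12 are also shown.

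**1. The plan's own power at 8:8.** Design effect = 1 + (16 − 1) × ICC, which is 1.75 at ICC 0.05 and 1.15 at ICC 0.01. With a and b services per arm, SE = √[DE/(16a) + DE/(16b)] and power = Φ(0.5/SE − 1.96).
- ICC 0.05: SE = √(2 × 1.75/128) = 0.1654, power 0.856 (stated 0.87).
- ICC 0.01: SE = √(2 × 1.15/128) = 0.1340, power 0.962 (stated 0.96).

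The stated power is reproduced to within 2 points. The stated effective sample sizes of 200–254 are not: 256/1.75 = 146 and 256/1.15 = 223. That is a separate matter and does not affect what follows.

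**2. Chance of 8:8 with freely drawn blocks.** Let h(s) be the probability that a block ends at position s, so h(s) = [h(s−2) + h(s−4) + h(s−6)]/3 with h(0) = 1. This gives h(10) = 0.498, h(12) = 0.516 and h(14) = 0.490. The last block then falls into one of these cases:

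| Last block starts after | Size drawn | Places used | Probability | Unequal, given this case |
|---|---|---|---|---|
| 10 | 6 | 6 | 0.1660 | 0 |
| 12 | 4 | 4 | 0.1719 | 0 |
| 12 | 6 | 4 | 0.1719 | 1 − 9/15 = 0.40 |
| 14 | 2 | 2 | 0.1634 | 0 |
| 14 | 4 | 2 | 0.1634 | 1 − 4/6 = 0.33 |
| 14 | 6 | 2 | 0.1634 | 1 − 9/15 = 0.40 |

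P(unequal) = 0.0688 + 0.0545 + 0.0654 = 0.189, so P(8:8) = 0.811 (exactly 15971/19683). The only unequal split possible is 9:7 or 7:9. Simple randomisation would give 8:8 in C(16,8)/2^16 = 12870/65536 = 19.6% of cases.

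**3. Cost of 9:7.**
- ICC 0.05: SE = √(1.75/144 + 1.75/112) = 0.1667, power 0.851 against 0.856.
- ICC 0.01: SE = √(1.15/144 + 1.15/112) = 0.1351, power 0.959 against 0.962.

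The loss is 0.5 and 0.3 points. With a t test on 14 degrees of freedom it is 0.6 and 0.4 points (0.803 to 0.797; 0.934 to 0.930).

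**4. SEIFA balance, given 8:8.** With eight services per quartile, the chance that k first-quartile services go to one named arm is C(8,k)²/12870.
- 4:4: 4900/12870 = 0.381.
- 5:3 either way: 2 × 3136/12870 = 0.487.
- 6:2 or worse: 2 × (784 + 64 + 1)/12870 = 1698/12870 = 0.132.

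In each row below the arms differ by at least four first-quartile services.

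| First-quartile services | Split | Probability |
|---|---|---|
| 8 | 6:2 or worse | 0.132 |
| 6 | 5:1 or worse | 0.119 |
| 4 | 4:0 | 0.077 |

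**5. What such a split could do.** A difference of four services out of eight per arm shifts the unadjusted arm difference by 4/8 = 0.5 of the quartile effect. The article gives no quartile effect. If it were 0.1 to 0.4 SD (assumed), the shift would be 0.05 to 0.20 SD, against a target of 0.5 SD. Using the baseline score would remove part of this.

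**The case against.** A reader might infer that blocks of 2, 4 and 6 contradict the 8:8 design or cannot deliver it. The article does not support that. There are 81 ordered block sequences that total 16, for example 6+6+4 or 6+4+4+2, and any of them gives 8:8 with certainty. How the list is closed is a detail that an article may leave to the full protocol. The 19% rests on an assumed generating rule, and the loss of power is negligible even then. All of this stands and makes the block question minor.

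A reader might also infer that varying block sizes serve no purpose because every service is enrolled first. The article says only that baseline precedes randomisation, while invitations run one after another down a list. Staggered allocation is not excluded, and varying block sizes would then help concealment.

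On SEIFA, unstratified cluster randomisation is valid, and chance imbalance is not bias. Eligibility already narrows the range to two quartiles. The Background lists several socio-economic and environmental factors and does not rank socio-economic status first, so it cannot be called the main determinant on the plan's own terms. Nothing shows that service postcode quartile predicts outcome within this range. The outcome is measured at baseline and family-level status is collected (Demographics). A covariate may also be named in an analysis plan that is not at hand. These points reduce the concern to a risk. They do not remove the case for using, at almost no cost, a service-level factor already held.

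Finally, the two parts pull against each other if handled carelessly. Stratifying by quartile with the same free blocks would lower P(8:8) to about 0.66 (strata of 8 and 8), 0.70 (6 and 10) or 0.49 (7 and 9). Equal numbers per arm are also impossible within an odd-sized stratum. The remedy has to allow for both.

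**Conclusion.** The point holds as a recommended improvement, not as an error in the plan. The described procedure does not by itself ensure 8:8. Under freely drawn, equally likely block sizes cut at 16, the split is 9:7 about 19% of the time, at a cost of roughly half a point of power or less. One sentence would settle it.

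The SEIFA part carries more weight. With 16 clusters and eight services per quartile (assumed), about 13% of 8:8 allocations are 6:2 or worse; a difference of that size has probability 8% to 12% if only four to six services come from the first quartile. It is a risk of imbalance in a given realised allocation. How much it matters depends on the prognostic strength of quartile, which the article does not state.

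**What to change.** - **If all 16 services are enrolled before any is allocated:** have the independent statistician make one draw from the full list, constrained to 8:8 overall and balanced by SEIFA quartile as closely as stratum sizes allow. Where a stratum is odd, let the arms differ by one service within it. Strata of 7 and 9, for example, can be split 3:4 and 5:4, which still totals 8:8. Include quartile as a fixed effect in the primary model.
- **If allocation is staggered or already done:** pre-specify SEIFA quartile as a covariate in the primary model, before outcome data are seen. The registration is described as retrospective, so this may be the applicable route. If an analysis plan already does so, nothing more is needed on this part.
- **If the block scheme is kept:** state that the block sizes are chosen to total 16.

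**Cost.** One short paragraph and, where still possible, a new allocation list, which requires the services to be listed first. The covariate uses one between-service degree of freedom (16 − 2 = 14 becomes 13), moving the two-sided 5% critical value from 2.145 to 2.160. If quartile proves unrelated to outcome, that small loss buys nothing; if it is prognostic, precision and balance both improve.
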